### Data collection methods and management

The study researchers have followed Castor training workshops and have followed the Basic Course Regulation and Organization for Clinical Investigators. The study researchers will obtain informed consent from potential trial participants. An identification code is assigned to the patient. The key to the code is safeguarded by the researcher. All data will be recorded in Case Report Forms (CRF) in Castor. If a participant terminates the trial early, the reason for dropping out, if provided, will be documented. Only the researchers will have access to the final trial dataset.

### Economic evaluation

An economic evaluation will be performed with a health care perspective according to the Dutch national guidelines for economic evaluation [41]. The time horizon of the economic evaluation will correspond to the trial follow-up of 6 months. A cost-effectiveness and a cost-utility analysis will be conducted. Incremental cost-effectiveness ratios will be calculated by dividing the difference in mean costs by the difference in mean effects of the intermittent and continuous esketamine treatment groups. For the effects, the parameters pain intensity measured by the NRS pain score and the Global Perceived Effect [20] will be used. Cost-utility will be based on the EQ-5D-5L [21] and expressed in costs per quality-adjusted life years (QALYs). Bootstrapping techniques will be used to estimate statistical uncertainty and the multiple imputation by chained equation approach will be used for missing data in the economic evaluation.

Healthcare utilization includes hospitalizations, outpatient visits, procedures, diagnostic tests and the prescription of pain medication. These data will be gathered during the prospective study. The costs of healthcare utilization will be valued using Dutch standard costs and prices provided by professional organizations such as the National Health Care Institute if standard costs are not available. The costs of medication will be valued using the prices of the Royal Dutch Society of Pharmacy.

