### Recruitment, allocation and blinding

CRPS patients who are selected for a treatment with intravenous esketamine will be placed on the regular clinical waiting list of the Center for Pain Medicine. Patients will be selected chronologically from this waiting list for esketamine treatment and are contacted by a researcher for trial information. The expected duration of the study inclusion period will be approximately 3 years. The first patients will be included in 2022. Patients can withdraw from the study at any time without giving reasons. This is without any consequences for further medical treatment. Patients who are not willing to participate in this study will receive standard care (inpatient esketamine infusions).

After informed consent, patients will be enrolled and randomized using Castor software (Castor EDC). Previous treatments with esketamine may influence the outcomes of this clinical trial and therefore stratified randomization is performed with randomization blocks according to whether patients received previous esketamine treatment. The randomization will be done with an allocation ratio 1:1. The patients, researchers and statistician will not be blinded during the data collection and analysis. The researcher will enroll patients and will assign patients to the interventions after randomization.

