
**Table 2 Tab2:** Questionnaires used in KetCRPS-2 study. *Adapted from the Core Outcome Measurement set for complex regional PAin syndrome Clinical sTudies (COMPACT)* [19]

COMPACT questionnaires [19]	Details	Study period assessed
Global Perceived Effect (GPE) [20]	The Global Perceived Effect asks the patient to rate, on a numerical scale, how much their condition has improved or deteriorated since some predefined time point.	T2, T3, T4
PROMIS-29 Profile version 2.1 [29]	Assesses 7 domains, each with 4 questions: depression, anxiety, physical function, pain interference, fatigue, sleep disturbance, and ability to participate in social roles and activities.	T0, T3
Short-form McGill Pain Questionnaire-2 (SF-MPQ-2) [30]	Six neuropathic items capturing the quality of pain	T0, T3
Pain Catastrophizing Scale [31]	To measure how catastrophizing affects the pain experience.	T0, T3
EQ-5D-5L [21]	To measure health state, comprising mobility, self-care, usual activities, pain/discomfort, anxiety/depression	T0, T3, T4
Pain Self-Efficacy Questionnaire [32]	The respondent considers how confident they are performing each activity, while taking their pain into account	T0, T3
CRPS severity score [14]	CRPS symptoms and signs based on the Budapest diagnostic clinical criteria	T0, T3

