### Statistical methods

Descriptive statistics are used to determine the frequency distributions of demographic variables, and to describe measures of central tendency and of dispersion, dependent on the shape of their distribution. The Shapiro-Wilk test is used to analyze whether or not continuous parameters are normally distributed. The effects of the treatment on the different study parameters will be evaluated with regression models to account for the stratification factor, received esketamine treatment in the past, in the randomization process. Continuous outcomes will be analyzed with a linear regression model, where the residuals will be evaluated for normality. In case of a violation of the assumption, (logarithmic) transformations will be applied. Count outcomes will be analyzed with Poisson regression models and binary outcomes with logistic regression models. For repeated measurements mixed effects, models will be used to account for correlations from measurements within the same patient. No correction of the rejection zone will be made for multiple comparisons, because of the more explorative nature of the analyses of the secondary and other parameters. All analyses will be conducted in accordance with the intention-to-treat principle. Data will be analyzed using the latest version of SPSS and R.

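### The stated economic analysis makes no use of baseline EQ-5D-5L utility when estimating the QALY difference, although it is collected; adjusting for it would be a nearly free gain in precision

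*Protocol article*

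**What the plan says.** Under Economic evaluation, the protocol article defines the incremental ratio in terms of arm means: "Incremental cost-effectiveness ratios will be calculated by dividing the difference in mean costs by the difference in mean effects". The effects are NRS pain and the Global Perceived Effect; for cost-utility they are QALYs derived from the EQ-5D-5L. On the horizon it says: "The time horizon of the economic evaluation will correspond to the trial follow-up of 6 months". On uncertainty and missing data it says: "Bootstrapping techniques will be used to estimate statistical uncertainty and the multiple imputation by chained equation approach will be used for missing data". No adjustment model, utility tariff or QALY formula is given.

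Table 2 lists the EQ-5D-5L and its time points: "To measure health state, comprising mobility, self-care, usual activities, pain/discomfort, anxiety/depression T0, T3, T4".

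Under Statistical methods, treatment effects are to be "evaluated with regression models to account for the stratification factor, received esketamine treatment in the past, in the randomization process". That is the only covariate named in the article. It matches the design, in which "stratified randomization is performed with randomization blocks according to whether patients received previous esketamine treatment". Utility is not a stratification factor. The Outcomes section closes by saying that later evaluations are compared with baseline, but attaches no model to this.

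**The concern.** A QALY differs from an outcome read at one visit. When utility is measured at the start, middle and end of the horizon, the usual construction includes the starting value. An arm that happens to begin with higher utility then collects more QALYs before treatment has done anything. It collects more again because utilities within a patient are correlated. Randomisation balances this only on average, and about 30 patients per arm leaves room for a visible gap.

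The effect matters most when the true QALY difference is small. The Sample size section expects the same NRS improvement in both arms (8.0 to 6.0). If utility behaves similarly, the denominator of the cost-utility ratio is expected to lie near zero, and a chance baseline gap can decide its sign. Bootstrapping an unadjusted difference describes that noise but does not remove it.

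**Working it through.** The article gives no figure for QALYs, utility variability or the precision of the economic evaluation. There is therefore no figure of the plan's own to reproduce on this point; its sample size calculation concerns NRS only.

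**Inputs from the article.** EQ-5D-5L at T0, T3 and T4 (Table 2), taken as 0, 3 and 6 months (Participant timeline); 6-month horizon (Economic evaluation); 60 patients (Sample size) allocated 1:1 (Recruitment, allocation and blinding), so 30 per arm.

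**Assumptions, not in the article.** Area-under-the-curve QALYs by the trapezoid rule; utility SD between 0.15 and 0.30, equal at all visits; between-visit correlation r of 0.3 to 0.7.

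**Step 1: weight of T0.** In years, QALY = 0.125·[U(T0) + U(T3)] + 0.125·[U(T3) + U(T4)] = 0.125·U(T0) + 0.25·U(T3) + 0.125·U(T4). The weights sum to 0.5, so T0 carries 0.125/0.5 = 25%.

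**Step 2: variance explained by T0 utility, equal correlation between visits.**
- V = Var(QALY)/SD² = 0.125² + 0.25² + 0.125² + 2r(0.03125 + 0.03125 + 0.015625) = 0.09375 + 0.15625r
- Slope of QALY on T0 utility: b = 0.125 + 0.375r
- Proportional cut in variance from adjustment: R² = b²/V

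| r | V | b | R² | SE ratio √(1−R²) |
|---|---|---|---|---|
| 0.3 | 0.1406 | 0.2375 | 0.40 | 0.77 |
| 0.5 | 0.1719 | 0.3125 | 0.57 | 0.66 |
| 0.7 | 0.2031 | 0.3875 | 0.74 | 0.51 |

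Even at r = 0 the cut is 0.015625/0.09375 = 17%, because T0 is itself part of the sum. These percentages do not depend on the SD.

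**Step 3: the same if correlation decays with time** (T0 with T4 is r²). V = 0.09375 + 0.125r + 0.03125r² and b = 0.125 + 0.25r + 0.125r².
- r = 0.3: 0.2113²/0.1341 = 33%
- r = 0.5: 0.2813²/0.1641 = 48%
- r = 0.7: 0.3613²/0.1966 = 66%

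**Step 4: standard error, for example SD 0.25 and r = 0.5 with equal correlation.** Unadjusted: 0.25·√(0.1719·2/30) = 0.027 QALY. Adjusted: 0.027·0.66 = 0.018. A small-sample factor of √(1 + 1/56) does not change the rounded value.

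**Step 5: effect of a chance baseline gap.** One standard error of the T0 difference is SD·√(2/30), which is 0.039 at SD 0.15 and 0.077 at SD 0.30. Multiplied by b, it moves the unadjusted QALY difference by 0.2375·0.039 = 0.009 up to 0.3875·0.077 = 0.030. The part passing directly through the T0 term is 0.125 times the gap, 0.005 to 0.010. The most that utility of 1 throughout could yield over the horizon is 0.5 QALY.

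**The case against.** The strongest reply is that the article is silent rather than wrong. It never says that the difference is raw or unadjusted. A regression-adjusted arm difference is still a difference in mean effects, and it can be bootstrapped and multiply imputed as planned. A condensed article may also leave health-economic model detail to a fuller plan. This stands in part: a reader might infer that the article has chosen to reject baseline adjustment, and the text does not support that. What remains is that the article does state an estimator, an uncertainty method and a missing-data method, and names one covariate elsewhere. An analyst who follows that text has no direction to use T0 utility.

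Four further limits stand in full:
- A reader might infer bias. Under randomisation the unadjusted difference is unbiased, and its bootstrap interval already includes chance baseline variation. Only precision and imbalance in the realised sample are at issue.
- A reader might infer that the economic analysis ignores the stratification factor. The Statistical methods sentence speaks of study parameters generally, and costs and EQ-5D-5L are among the listed secondary parameters. It can be read as covering them.
- That T0 enters the QALY is inferred from the measurement schedule, since no formula is given.
- It is tempting to turn the variance cut into power. The article plans no hypothesis test on QALYs, so such figures would have no referent.

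**Conclusion.** The point holds as an improvement to a secondary analysis, not as an error in the document. As stated, the economic evaluation makes no use of T0 EQ-5D-5L utility in estimating the QALY difference, although the data are collected. If QALYs are area-under-the-curve values, adjustment would cut the variance of the difference by about 40% to 74% for equal correlations of 0.3 to 0.7. If correlation decays with time, the cut is about 33% at 0.3 and 48% at 0.5. The direction is secure under any of these assumptions; the size is not, because the article supplies neither a utility SD nor a correlation. Nothing has been computed for costs or for the ratio itself, so the claim is confined to the QALY denominator.

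**What to change.** In Economic evaluation, state that the incremental QALY is the arm coefficient from a linear regression of QALY on arm, T0 EQ-5D-5L utility and prior esketamine. State that the incremental NRS effect comes from the same model with T0 NRS in place of T0 utility. The Global Perceived Effect has no T0 value in Table 2, so a baseline term does not apply to it. Fit the models within each bootstrap sample and each imputed data set, and take the incremental effects and their uncertainty from the adjusted differences. Keep the raw arm means as a descriptive table. Add one sentence giving the QALY formula, so that the role of T0 is explicit.

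The cost is one or two degrees of freedom and a few lines of code. All variables are already collected, so no visit or patient is added. Because patients, researchers and statistician are all unblinded, the choice is best written down before outcome data are examined.

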### Monitoring

Monitoring of the data will be performed by an independent monitor. A data safety monitoring board is not needed since this study poses a negligible risk.

Adverse events will be assessed during study visits by the researchers, including the probability that adverse events are associated with the treatment in this study. All adverse events reported spontaneously by the patient or observed by the researchers or clinicians will be recorded. Serious adverse events (SAEs) will be reported within 15 days after they are reported to the researchers. SAEs will be followed until they resolve or reach a stable non-serious level. Depending on the event, follow up may require additional tests or referral to the general physician or a medical specialist.

## Discussion

There is evidence that esketamine infusions can provide clinically effective pain relief in a subgroup of CRPS patients with refractory pain [10, 11]. To our best knowledge, intermittent and continuous esketamine treatments have never been compared in RCTs. This article describes the rationale and design of an RCT that assesses the differences between intermittent and continuous intravenous esketamine treatments in CRPS patients. This study will provide information on whether 6 intermittent outpatient esketamine infusions are non-inferior to a 6-day inpatient continuous esketamine infusion.

As an alternative to lengthy inpatient hospital admissions, an outpatient treatment regimen with multiple clinic visits could be proposed [16, 42–45]. If our study reveals non-inferiority of intermittent versus continuous esketamine infusions, these findings can be beneficial to increase the availability of treatment with esketamine infusions. In addition, patient burden can be reduced by offering esketamine in a more flexible day-care treatment compared to a 6-day consecutive hospital admission. Economic evaluation may show that intermittent outpatient esketamine treatments are more cost-effective.

In this RCT, the intermittent outpatient treatment protocol was defined as 6 day-care esketamine infusions every 2 weeks for 3 months. Our research group decided to incorporate 6 outpatient day-care infusions in our outpatient treatment protocol because our inpatient treatment protocol also consists of 6 days. In addition, we decided to spread the 6 outpatient infusions over 3 months because pain relief is expected to last up to 3 months post-infusion [10, 22]. Furthermore, the intermittent 6 outpatient ketamine infusions over the course of 3 months might be a way to extend the pain relief as result of esketamine administration.

Regarding the intermittent infusion duration, our research group decided to administer esketamine for 6 hours. This is the longest infusion time possible in our outpatient clinic. Unfortunately, there is no gold standard for the duration of esketamine administration. Maher et al. noted that although the general trend is that longer durations of esketamine administration provide increased duration of pain reduction, there may be an optimal infusion duration of several hours beyond which no benefit is derived but the potential for side effects increases [42]. In addition, Noppers et al. described that infusion durations shorter than 2 hours were unlikely to accomplish pain relief for more than 2 days [46]. Furthermore, in 2 survey studies on esketamine in CRPS, the most often reported infusion duration was 4 hours [47] and 6 hours [5]. This is in line with the outpatient treatment protocol of the Center for Pain Medicine.

Regarding the esketamine dose, there is significant heterogeneity between published studies on CRPS [10, 11]. Most of the studies reported esketamine dose based on body weight, with doses ranging from 0.15 to 7.0 mg/kg/hour [11]. In both the inpatient and outpatient treatment protocol of the Center for Pain Medicine, the esketamine dose can be titrated from 0.05 to 0.2 mg/kg/hour. Although, this dosage scheme is relatively low compared to other studies [10, 11], we believe that high dosing of esketamine is not necessary to achieve sufficient pain relief. First, a retrospective study by our research group showed that the median effective esketamine dose in our population was 6 mg/h, which corresponds to 0.1 mg/kg/hour for a 60 kg patient [13]. Furthermore, it is suggested that the effective esketamine treatment for CRPS is not related to the actual dose or rate of the esketamine infusion, as low-dose esketamine regimes showed comparable duration of pain relief compared to high-dose esketamine regimens performed in intensive care units [42].

To predict the response to esketamine infusions more knowledge is required on mechanisms resulting in pain reduction by esketamine infusions [3, 13]. Multiple mechanisms of actions have been proposed for esketamine treatments [3, 48]. Interestingly, upon the termination of esketamine infusions, Sigtermans et al. showed that concentrations of esketamine and its metabolite norketamine rapidly declined [22]. Therefore, it is suggested that the long-lasting analgesic effect of esketamine in CRPS is not driven by pharmacokinetics of esketamine or norketamine [22, 49]. It is likely that long-lasting pain relief is the result of neurotrophic effects at spinal and supraspinal sites that effectively counteract central sensitization by prolonged NMDA receptor desensitization [22, 49]. In addition, the immunoregulatory effects of esketamine may interact with the affected and closely linked immune and nervous system in CPRS patients [7, 50]. For instance, recent studies on depression and comorbid pain described the immunoregulatory aspects of esketamine that may result in downregulation of peripheral pro-inflammatory cytokines and the attenuation of central glial cells [8, 51, 52].

The strengths of this study design are the randomized design and the stratification of patients based on whether they have had esketamine infusions in the past. Another strength of this study is that several objective parameters for esketamine treatments and the cost-effectiveness are assessed. Complementary to further understandings of esketamine mechanisms, diagnostic tests and biomarkers are needed to predict response on esketamine infusions for CRPS patients [13, 27, 53]. By incorporating a peripheral blood inflammatory parameter, conditioned pain modulation, thermography and QST, our research group hopes to provide information on differences between responders and non-responders to esketamine treatment. This paves the way to a more mechanism-based approach in selecting CRPS patient for esketamine treatment. A potential pitfall of the study protocol is that, although CRPS is a multi-mechanism syndrome, patients receive esketamine as a monotherapy. Targeting only a single mechanism might not be sufficient in CRPS [3]. Furthermore, patients cannot be blinded for an intermittent or continuous esketamine treatment. Of note, although the decisions of our research group on the treatment protocols for esketamine administration have been made after thorough consideration, significant uncertainty exists for the most ideal treatment regimen for esketamine infusions and may also differ for each individual CRPS patient. We acknowledge that all decisions on the length and dose of esketamine administration can influence the outcome parameters in this RCT.

## Data Availability

Not applicable.

## Abbreviations

AF: Alkaline phosphatase
ALT: Alanine aminotransferase
AST: Aspartate aminotransferase
COMPACT: Core Outcome Measurement set for complex regional PAin syndrome Clinical sTudies
CRF: Case Report Forms
CRPS: Complex Regional Pain Syndrome
GGT: Gamma-glutamyl transferase
IASP: International Association for the Study of Pain
LDH: Lactate dehydrogenase
MC: Medical Center
NMDA: N-methyl-D-aspartate
NRS: Numerical Rating Scale
QST: Quantitative Sensory Testing
RCT: Randomized Controlled Trial
SPIRIT: Standard Protocol Items Recommendations for Interventional Trials
